## Abstract

**Introduction:**

Statins are among the most widely used drugs. While they are effective for primary and secondary prevention of cardiovascular (CV) disease in middle-aged subjects, their benefits for prevention in older adults (aged ≥70 years) without CV disease are uncertain, particularly for those with multimorbidity. Statin side effects and drug interactions are common in older patients and may negatively impact quality of life. To date, the only randomised controlled trial (RCT) investigating statin discontinuation in older adults has demonstrated no difference in survival but did note a small improvement in quality of life for those who discontinued statins. However, this trial exclusively enrolled patients with a life expectancy <1 year. Therefore, the present RCT aims to assess the safety and potential benefits of statin discontinuation in primary prevention for the ever-growing population of multimorbid older adults.

**Methods and analysis:**

This study is a multicentre, randomised, non-inferiority trial conducted in both inpatient and outpatient settings in Switzerland, France and the Netherlands, targeting patients using statins for primary prevention. 1800 participants are randomly assigned 1:1 to either discontinue (intervention arm) or continue (control arm) statin therapy. The primary objective is to compare the primary composite endpoint of major CV events (non-fatal myocardial infarction or non-fatal ischaemic stroke) and all-cause death between the control and intervention groups over a follow-up duration of up to 48 months. We hypothesise that discontinuing statins does not result in shorter event-free survival, with a non-inferiority margin set at 5.2 weeks over a 2-year observation period. Secondary objectives are to compare patient-centred outcomes (health-related quality of life, muscle pain symptoms, falls and sarcopenia) and all-cause death, non-CV death, major CV events and coronary and peripheral artery revascularisation. The study is open-labelled, with blinded outcome adjudication of the primary endpoints.

**Ethics and dissemination:**

The trial protocol has received approval from the local ethics committees in Switzerland, France and the Netherlands. Results will be published in a peer-reviewed journal.

**Trial registration number:**

Clinicaltrials.gov: NCT05178420; BASEC (Swiss Ethics Commission): 2021-01513; FOPH (Swiss national portal): SNCTP000005172; Netherlands Trial Register: NL83907.058.23; France Trial Register: 22.04747.000158– IDRCB 2022-A02481-42.

STRENGTHS AND LIMITATIONS OF THIS STUDYThis study is the largest ongoing trial to assess the safety and potential benefit of statin discontinuation in multimorbid older adults, who are often excluded from major randomised controlled trials.In addition to cardiovascular endpoints, this trial assesses patient-centred outcomes important for older adults, such as quality of life, muscle pain, sarcopenia and falls as secondary endpoints.While outcome adjudication and ascertainment is blinded, the lack of participant and physician blinding may introduce bias in treatment adherence and subjective outcome assessments.We engaged patients in safety monitoring, recruitment strategies and dissemination efforts, which increases the study’s relevance and applicability in real-world settings.

## Introduction

### Background

 Statins are among the most widely used drugs.^1^ While they have been found to be effective for primary and secondary prevention of cardiovascular (CV) disease (CVD) in middle-aged subjects,^2^,^4^ their benefits for prevention in older adults without CVD remain uncertain, particularly for those over 70 years,^3 4^ and in those with several chronic diagnoses (multimorbidity) who are often excluded from clinical trials.^5^,^7^ First, among those aged ≥70 years, no consistent statin benefit for primary prevention was shown on all-cause mortality and CVD in randomised controlled trials (RCTs).^3 4 8^ Second, the majority of older adults suffer from multimorbidity (commonly defined as ≥2 chronic conditions),^9 10^ and most large RCTs on lipid-lowering therapies did not include multimorbid older adults.^6^ Moreover, individuals aged ≥70 years are under-represented in most RCTs, including those assessing statin benefits for prevention.^68 11^,^16^ Additionally, statin side effects and drug interactions are more likely to occur in older adults and patients with multiple medications and may negatively impact health-related quality of life (QOL).^17^,^21^ The proportion of older patients developing muscle pain under statins has been shown to be 5–20% in observational studies.^17 22 23^

While data supporting statin prescription for primary prevention in older multimorbid adults are limited, in practice, statins are often discontinued in multimorbid older adults without CVD due to side effects.^24^ Recent guidelines on this topic are conflicting. The American Heart Association/American College of Cardiology (AHA/ACC) Cholesterol Guidelines suggest that discontinuing statins may be reasonable when ‘functional decline, multimorbidity, frailty or reduced life-expectancy limits the potential benefits of statins’.^25^ Conversely, other guidelines consider statins in older adults with high CV risk while accounting for factors like frailty and patient preferences. They recognised that there are uncertainties about the benefits and harms of statins in those aged 75 years and older with comorbidities and cognitive impairment.^26^,^28^ Those are, however, expert opinions, not based on data from RCTs on statin discontinuation.

To this day, no RCT examining the benefits of statins in primary prevention has exclusively recruited older (≥70 years) multimorbid participants^6 29^; only a single RCT including participants with a short life expectancy (<1 year) found no difference in CV events and mortality between the groups, but found a slightly better health-related QOL among those who discontinued statins (mean McGill QOL score, 7.11 vs 6.85; p=0.04).^18^ Conversely, in a retrospective cohort study, older adults who discontinued statins for primary prevention were more often admitted to the hospital for a CV event, but interpretation of this data does not allow a causal conclusion, given the design and the lack of measurement of several CVD confounding factors and risk of confounding by indication, given that reasons for statin discontinuation were not reported,^30^ as illustrated by another retrospective cohort study with discontinuation. associated with a higher rate of CV events, but also larger risk of hip fractures and non-CV mortality.^31^ A recent literature review highlighted the importance of further RCTs.^32^

Therefore, the primary aim of this trial is to evaluate the safety of discontinuing versus continuing statin therapy in older adults with multimorbidity but no clinical CV disease.

## Methods and analysis

### Trial design

STatin discontinuation as pRevention among the Elderly And Multimorbid (STREAM) is an international, multicentre, randomised, non-inferiority, parallel and controlled trial. Study subjects are randomly assigned in a 1:1 ratio to either discontinue (intervention arm) or continue (control arm) statin and other lipid-lowering drug (LLD) therapies (figure 1 and table 1). This study protocol follows the Standard Protocol Items: Recommendations for Interventional Trials guidelines.^33^ The governance structure includes a steering committee and an international advisory board (online supplemental appendix 1). The sponsor, according to regulations, is Inselspital, Bern University Hospital.

**Figure 1 F1:**
[figure not shown]
Flowchart of the STatin discontinuation as pRevention among the Elderly And Multimorbid Study. ITT, intention-to-treat; PP, per-protocol.

**Table 1 T1:** Study population, intervention control and outcomes

Population	Older adults (≥ 70 years) with multimorbidity (≥ 2 chronic medical problems) and statin therapy in primary prevention.
Intervention	Patients will be randomised 1:1 into the intervention or control group. In the intervention group, statin therapy will be stopped from the next scheduled intake after randomisation. Additional lipid-lowering medication lowering LDL cholesterol (ie, ezetimibe, PCSK9 inhibitors, future novel lipid-lowering medications with lowering of LDL cholesterol demonstrated in randomised trials) will also be stopped in the intervention group.
Control	No control intervention is planned. In the control group, statin therapy will be continued as prescribed before the trial.
Outcomes	The primary outcome is a composite endpoint of major CV events (non-fatal myocardial infarction, non-fatal ischaemic stroke) and all-cause death over a follow-up duration of 2 years.Secondary outcomes are: All-cause death, non-CV death, major CV events, coronary and peripheral artery revascularisation. Geriatric-relevant questionnaires: EQ-5D questionnaire, verbal numeric pain rating score, falls, SARC-F questionnaire and Girerd Medication Adherence Scale.

CV, cardiovascular; EQ-5D, European Quality of Life 5-Dimensions; LDL, low-density lipoprotein; SARC-F, Strength, Assistance with walking, Rise from a chair, Climb stairs and Falls.

### Objectives

The overall aim of this study is to assess the safety of discontinuing statin therapy compared with continuing statin therapy in older adults with multimorbidity and without clinical CVD. The primary objective is to compare a composite endpoint of major CV events and all-cause death between the control and intervention groups.

The secondary aim is to compare the impact of statin discontinuation on geriatric symptoms. Specific secondary objectives also include all-cause death (including CV and non-CV deaths) and geriatric endpoints, such as falls, health-related QOL, muscle pain and sarcopenia.

### Study setting

The trial is conducted across multiple large hospitals and general practitioner (GP) practices in Switzerland, Bordeaux (France) and Leiden (Netherlands). Detailed information regarding specific study sites can be found in the official record on clinicaltrials.gov (NCT05178420). Multiple general practices also refer patients for enrolment to investigators’ sites.

### Eligibility criteria

Inclusion criteria are patients ≥70 years of age, with multimorbidity defined as ≥2 coexistent chronic conditions (besides dyslipidaemia) with an estimated history of 6 months or more based on clinical decision^10^ and taking a statin for ≥80% of the time during the year before baseline according to the patient. We did not include an upper age limit because we aimed to include all older patients to ensure broad generalisability of our findings.

Exclusion criteria are as follows:

Secondary prevention settings based on previous large statin trials^4 34^:History of myocardial infarction type 1 (Non-ST-elevation myocardial infarction/ST-elevation myocardial infarction)Stable angina pectoris with documented ischaemia on a stress test or with significant coronary disease defined as a coronary stenosis >50%.History of percutaneous coronary intervention (balloon or stent) or coronary artery bypass graft.History of unstable angina, defined as acute coronary syndrome symptomatic at rest, crescendo or new-onset angina (Canadian Cardiovascular Society Score 2 or 3) without ECG or cardiac biomarker changes (based on available documents).History of ischaemic stroke (this does not apply to clearly cardioembolic causes for stroke).History of transient ischaemic attack, defined as transient neurological deficit without diffusion restriction in MRI.History of carotid revascularisation (eg, stent, bypass, carotid thrombendarterectomy)History of peripheral arterial disease requiring revascularisation (eg, percutaneous transluminal angioplasty, stent, femoral thrombendarterectomy, bypass) or Fontaine IVAortic disease that required a vascular repair or aortic aneurysm with a maximum diameter >5.5 cm (men) or >5.2 cm (women) based on available documentsProbable familial hypercholesterolaemia based on Dutch lipid score ≥6 based on available documents (low-density lipoprotein cholesterol (LDL-C), family history, personal history)^35^Elevated risk of death within 3 months after baseline, defined as:Hospitalised patients planned for palliative care within 24 hours of admission.Hospitalised patients with a Palliative Performance Scale level <30%, based on the situation at least 1 month before hospitalisation, this corresponds to an estimated survival of 43% after 3 months.^36^Patients with an advanced metastatic cancer prognosis of ≤20% survival rate within 1 year after baseline (based on an online tool: https://cancersurvivalrates.com).Participation in a clinical trial with potential impact on the STREAM CV endpoints, based on clinical judgement.

Individuals with subclinical CVD, such as coronary sclerosis or carotid plaques, are not excluded, as they were not specifically included in large secondary prevention statin trials. We do not exclude patients with diabetes, as RCTs did not find clear benefits in primary prevention in patients beyond 70 years of age.^11 37^ Additionally, patients with cognitive impairment or psychiatric diseases are not excluded to increase generalisability.^38^

### Interventions

In the intervention group, statin therapy is stopped from the next scheduled intake following informed consent and randomisation. Additionally, all lipid-lowering medications (ie, ezetimibe, PCSK9 inhibitors, bempedoic acid and future novel lipid-lowering medications with lowering of LDL-C demonstrated in randomised trials) are also stopped in the intervention group. In the control group, statin therapy and other LLDs are continued as per usual care.

### Assessment of primary outcome

The primary endpoint is a composite endpoint of adjudicated major non-fatal CV events (non-fatal myocardial infarction, non-fatal ischaemic stroke) and all-cause death over a follow-up duration of at least 2 years. All-cause death (and not CV death only) was chosen to account for competing mortality among this multimorbid population and a possible shift from CV to other causes of death (such patterns were seen in two statin RCTs).^3 8 39^ The composite endpoint was selected to assess the net clinical benefit in this population with expected high mortality.

### Assessment of secondary outcomes

The following secondary outcomes will be evaluated:

All-cause death.Non-CV death.Major CV events (CV death, non-fatal myocardial infarction and non-fatal ischaemic stroke).Total CV events (CV death, non-fatal myocardial infarction, hospitalisation for unstable angina, non-fatal ischaemic stroke (including TIA) and arterial revascularisation (coronary and peripheral urgent and non-urgent revascularisation)).Total composite events (all-cause death, non-fatal myocardial infarction, hospitalisation for unstable angina, non-fatal ischaemic stroke (including TIA) and arterial revascularisation (coronary and peripheral urgent and non-urgent revascularisation)).Sarcopenia parameters, measured by Strength, Assistance with Walking, Rising from a Chair, Climbing Stairs and Falls Questionnaire at 12 months, 24 months, 36 months and 48 months.^40 41^Girerd medication adherence scale at 0 months, 12 months, 24 months, 36 months and 48 months.^42^EQ-5D Questionnaire at 3 months, 12 months, 24 months, 36 months and 48 months.^43^Verbal Numeric Pain Rating Score at 3 months.^44 45^Self-reported falls at 12 months.

As the only previous RCTs evaluating statin discontinuation in older adults showed slightly increased QOL,^18^ these geriatric questionnaires were added to evaluate the impact of statin discontinuation on geriatric syndromes. We will collect sociodemographic data, including marital status and receipt of formal or informal caregiving support. Additionally, at baseline, we will assess frailty using the FRAIL Scale^46^ and cognitive function using the Six-Item Cognitive Impairment Test Score.^47^ This will allow for secondary analyses and exploration of potential effect modifiers in our results.

### Study duration

The expected recruitment duration is about 36 months. Study participants remain in the study for the entire duration of the intervention period. Minimum intervention period duration is 12 months, and the maximum intervention period duration is 48 months. The mean intervention period is expected to be 24 months.

### Follow-up

Follow-up visits will be conducted at 3 months and 12 months after randomisation, then yearly until end of study with a maximum follow-up of 48 months after randomisation. Study personnel will contact the participant and/or GPs by phone and will review medical records to obtain information from hospitals and GPs about medical events and drug treatments during follow-up. We will collect the dosage and frequency of lipid-lowering agents. For concomitant CV treatments, the drug names will be recorded and if they have been established since baseline or started within any of the follow-up periods. At each yearly follow-up call, we will assess the Girerd Medication Adherence Scale. This approach enables continuous monitoring of intervention adherence throughout the study. Additionally, patients and their GPs will be reminded of the randomisation assignment after each follow-up call and instructed to inform the study personnel of any changes in lipid-lowering treatment. Medication adherence will be further assessed with a lipid-level measurement in 100 patients per group at the 1-year follow-up. Patients are not excluded if they are hospitalised during the follow-up period; all participants remain in the study regardless of hospitalisation. All hospitalisations are recorded within the safety reporting, and those potentially related to a CV event or death are adjudicated to ensure accurate outcome assessment.

### Sample size

The sample size calculation is based on a non-inferiority design where we test whether discontinuing statins does not result in reduced event-free survival time (primary endpoint) up to a certain degree (non-inferiority margin). The primary effect measure will be the difference in the restricted mean event-free time over 24 months between the two arms.^48 49^

We defined the non-inferiority margin on the absolute scale of integrated risk difference and fixed it at 5% over 24 months of follow-up. This can be interpreted as follows: we want to exclude a loss in event-free time of more than 2 ½ weeks per year (or about 1.5 days per month) over a 2-year observation period (5.2 weeks overall). This difference was considered clinically irrelevant (=non-inferior) given the multimorbid study population with a high event and death risk by all project partners and our international advisory board (online supplemental appendix 1).^50^

Based on preliminary data in the beginning of 2020 from our OPERAM trial that also randomised a multimorbid population over 70 years old,^38 51^ we estimated the primary event probabilities in the control group at landmark time points as follows: 22% at 12 months, 34% at 24 months and 43% at 36 months; a drop-out rate of 2% over 1 year was observed.^38^ With 1800 participants, we will achieve a power of 89% in the intention-to-treat (ITT) and 83% in the approximated per-protocol (PP) analysis set at a one-sided α level=0.025.

### Recruitment

The participating study centres screen their electronic patient records in line with the local regulations on data protection for patients fulfilling the eligibility criteria. GP practices have also been contacted and asked to screen and inform their patients about the possibility to participate in the study. Patient and public involvement in recruitment is described in the corresponding section. For screened patients who do not consent to participate, the local sites are advised to collect age, gender, eligibility criteria assessment and the reason for not consenting systematically in the electronic case report form to assess the degree of potential selection in the study enrolment process.

### Allocation

Participants are randomised in a 1:1 ratio to either discontinuing statin versus continuing statin, with stratification according to age (categorised into two groups: cut-off <75/≥75 years of age), statin intensity (categorised into high, moderate and low intensity)^25^ and time under statin before inclusion (cut-off: ≤6/>6 years, as 6 years is the longest follow-up in statin trials published in the CTT meta-analysis)^4^ using computer-generated randomly permuted blocks of varying size. Randomisation is implemented in a web-based system that also hosts the electronic case report form. Participants are only randomised after eligibility criteria have been checked and informed consent provided (online supplemental appendix 2: participant consent form). Randomisation lists were generated by an independent statistician who is otherwise not involved in the trial and only accessible by data managers who are not involved in any enrolment activities.

### Blinding

This trial is designed as an open-label study, with blinded outcome ascertainment and adjudication.

Regular telephone calls are made by partially blinded study nurses. Partial blinding means that study personnel initially assess participants’ outcome events over the phone without knowledge of their group assignment. This includes some subjective secondary outcomes, such as muscle pain. Blinding is maintained until the assessment of medication compliance, at which point group allocations become known. The primary outcome is also adjudicated by a blinded clinical event committee (CEC) (see Harms section). Blinding participants and treating physicians was deemed unfeasible for several reasons. First, providing multiple placebo tablets of identical appearance and taste for every statin agent and dosage would be impractical and costly. Second, medication changes to a standard dosing of statins in an older population might lead to increased risks of non-adherence and medication-related adverse events.^52^

Pragmatic studies often avoid placebos intentionally, aiming to assess the difference between an intervention and the best current usual treatment. Most large RCTs on deprescribing do not use placebos.^18 53^

### Data collection and management

For each enrolled trial participant, an electronic case report form is maintained, using a dedicated EDC system (https://webspirit.systems/).

### Statistical methods

The primary statistical analysis of the trial will be done at CTU Bern, based on well-established standard operating procedures. Details are specified in a statistical analysis plan (SAP) that has been finalised before all patients are enrolled.

The primary outcome of STREAM is analysed with a flexible parametric survival model with all stratification factors as covariates. The difference in restricted mean event-free time over 2 years will be the effect measure.^48 49^ A 2-year period was chosen, as this is the average follow-up time in this trial and a clinically relevant timeframe given the old multimorbid patient population with expected high mortality by expert consensus of the steering committee and our international advisory board. Two analysis sets are used for the primary analysis as described below. Non-inferiority will be declared if, for both ITT and PP analysis sets, the one-sided 97.5% CI does not cross the non-inferiority margin. We acknowledge that any choice for the non-inferiority margin is to some extent subjective, and a margin that is universally agreeable is not achievable, especially in this heterogeneous patient population.^54 55^ Components of the primary outcome and other time-to-event outcomes are analysed with the same methods as the primary outcome. Effects on time-to-event outcomes may also be presented as HRs. Continuous outcomes will be analysed using linear regression with baseline values and stratification factors as covariates and mean difference as effect measure.

ITT and PP analyses will be performed. The ITT analysis set consists of all randomised patients in the allocated group regardless of any protocol violations or crossover. For the PP analysis set, we defined criteria in the SAP for protocol adherence and postrandomisation factors that might cause confounding/selection bias.^56^ For this, we considered prerandomisation and postrandomisation factors that are predictive of adherence, amount of statin intake that constitutes adherence to each arm, crossovers, other CV active medication and intercurrent events. Patients who deviate from their assigned treatment for more than two consecutive months will be classified as crossovers. Rather than excluding these individuals from the PP analysis and introducing selection bias, their contribution to the final model will be down-weighted using inverse probability weighting. The 2-month threshold was selected because exact start and stop dates of treatment deviations cannot be reliably determined from follow-up calls. This corresponds to an adherence rate of 80%, which is considered sufficient.^57 58^ Moreover, given that the effects of statin therapy on risk are not immediate, a temporary interruption of this duration is considered tolerable.^38 59^ PP analyses will be done using g-methods adapted to estimate the restricted mean event-free time.^60^

Participants without a time-to-event outcome reported as a serious adverse event (SAE) will be assumed not to have had an event. Dropouts and loss to follow-up will be censored at the time point of the dropout. For other endpoints, multiple imputation will be considered if the proportion of missing data is between 5% and 40%.^61^ Multiple imputation will use logistic regression for binary outcomes and predictive mean matching otherwise. 50 imputation datasets will be created and results pooled using Rubin’s rule. Imputation models will use treatment group, selected baseline parameters as well as selected endpoints. Times until events occurred will not be used, but the binary indicators may be used in the models.

Subgroup analyses will be performed by statin intensity, statin duration, sex, age, frailty, history of diabetes, recruitment source, CV risk, smoking status, degree of multimorbidity and hypertension. However, given the limited accuracy of life expectancy models in older, multimorbid patients, we chose not to use life expectancy but rather stratify the analysis according to their age.^62^

The SAP will outline the approach for addressing co-interventions using sensitivity analyses.^63^

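### The primary ITT model, as the article describes it, names no covariate beyond the stratification factors; adding prognostic baseline data already collected could gain some precision

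*Protocol article*

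**What the plan says.** Protocol article, Statistical methods: the primary outcome "is analysed with a flexible parametric survival model with all stratification factors as covariates". The Allocation section defines the factors as "age (categorised into two groups: cut-off <75/≥75 years of age", statin intensity in three levels, and time on statin up to or beyond 6 years. Setting and country are not among them.

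The Sample size section fixes the effect measure: "The primary effect measure will be the difference in the restricted mean event-free time over 24 months between the two arms". The margin is stated on that scale; the authors "fixed it at 5% over 24 months of follow-up". Stated power with 1800 participants is 89% for ITT and 83% for an approximated per-protocol (PP) set, at one-sided 0.025. Both sets must meet the margin.

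Other baseline data are available. Under Assessment of secondary outcomes, "at baseline, we will assess frailty using the FRAIL Scale", for use in secondary analyses and the study of effect modifiers. Statistical methods adds: "Subgroup analyses will be performed by statin intensity, statin duration, sex, age, frailty, history of diabetes, recruitment source", among others. For PP, the same section says that factors from before and after randomisation that predict adherence were considered, with inverse probability weighting and g-methods. Further detail is left to a finalised SAP, which is not at hand.

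**The concern.** The composite counts death from any cause in people aged 70 and over with no upper age limit, recruited as inpatients, outpatients and through general practice in three countries. Baseline risk is likely to vary widely. Of the named factors, a two-level age term is the one most likely to be prognostic, and it places everyone aged 75 or over in one group. How well statin intensity and time on statin predict death is not documented.

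The RMST difference is a marginal, collapsible measure. Standardising over baseline covariates therefore leaves the estimand unchanged, and prognostic covariates reduce its variance. What is at stake is the width of the confidence interval that is compared with the non-inferiority margin. The argument does not carry over to the hazard ratios that the article may also present, because adjusting those changes the quantity estimated.

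**Working it through.** **1. Inputs from the article.** Control event probabilities of 22%, 34% and 43% at 12, 24 and 36 months; drop-out of 2% per year; follow-up of 12 to 48 months; 900 per arm; one-sided 0.025. Margin: 0.05 × 24 = 1.2 months, or 5.2 weeks.

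**2. Reproducing the stated ITT power without covariates.** Take a piecewise-exponential event-free curve through 1, 0.78 and 0.66 at 0, 12 and 24 months.

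- RMST(24) = 12 × 0.22 / ln(1/0.78) + 12 × 0.12 / ln(0.78/0.66) = 10.63 + 8.62 = 19.25 months.
- The SD of event-free time truncated at 24 months is 7.70. With drop-out and follow-up spread uniformly over 12–48 months, the asymptotic SD is 7.77.
- Power = Φ(1.2 / √(2 × 7.77² / 900) − 1.96) = Φ(1.2 / 0.366 − 1.96) = Φ(1.32) = 90.6%.
- With drop-out only it is 90.8%; with drop-out and follow-up uniform over 12–36 months it is 90.4%.

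All are within 2 points of the stated 89%, so that figure is reproduced. The 83% for PP was not, because the article does not describe the approximation behind it.

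**3. Size of a possible gain.** This needs prognostic strengths that the documents do not give, so they are assumed. In each scenario 400,000 participants were simulated, with the hazard scaled to 66% event-free at 24 months. Further assumptions:

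- age is 70 plus a gamma variable (shape 2, scale 3.8), capped at 98;
- frailty is binary, with prevalence 15% at age 70 rising 1.5 points per year;
- sex is split 55/45 and recruitment source 50/50.

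R² is from linear regression of min(T, 24) on the covariates. Variance ratio = (1 − R² full) / (1 − R² age cut at 75). Power is calibrated to the stated 89%: Φ((1.960 + 1.227) / √ratio − 1.960).

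| Assumed HR: age per 5 years / frailty / sex / source | R², age cut at 75 | R², full | Variance ratio | ITT power |
|---|---|---|---|---|
| 1.2 / 1.3 / 1.2 / 1.2 | 0.6% | 2.4% | 0.982 | 89.5% |
| 1.35 / 1.6 / 1.3 / 1.5 | 1.7% | 7.3% | 0.943 | 90.7% |
| 1.5 / 2.0 / 1.4 / 2.0 | 2.8% | 14.4% | 0.881 | 92.4% |
| 1.5 / 2.5 / 1.4 / 2.5 | 2.9% | 18.2% | 0.842 | 93.5% |

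Example, last row: (1 − 0.182) / (1 − 0.029) = 0.842; 3.187 / √0.842 − 1.960 = 1.513; Φ = 93.5%.

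The variance falls by 2% to 16%. The interval narrows by 1 − √0.982 = 0.9% to 1 − √0.842 = 8.2%. The equivalent sample size is 1800/0.982 ≈ 1833 to 1800/0.842 ≈ 2138. Replacing the age cut by continuous age alone cuts the variance by 1–5% (ITT power 89.3–90.6%).

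A second set of assumptions (source HR 1.5 / 2 / 2.5, FRAIL 1.15 / 1.25 / 1.35 per point, age 1.05 / 1.07 / 1.08 per year, sex 1.2 / 1.3 / 1.4) gave reductions of 4%, 9% and 14%, and ITT power of 90%, 92% and 93%. This lies inside the same range.

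**The case against.** The strongest reply is that nothing here is wrong. Adjusting for the stratification factors is standard and valid, and the trial reaches its stated ITT power with no covariates at all. That stands, and it limits the point to an optional improvement.

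Four stronger readings are tempting, and the documents do not support them.

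- **That the model excludes every other covariate, or that age must enter it as two levels.** The article names the stratification factors and no others. It does not rule out further terms, and the age cut-off is given as a randomisation stratum. The SAP may already add covariates or use continuous age.
- **That PP power would rise in the same way.** PP already considers baseline factors through weighting and g-methods, so a strata-only PP comparator is an assumption. The ITT variance ratio cannot simply be applied to a weighted estimator, and the basis of the 83% is not described.
- **That not stratifying by setting or country biases the result.** Chance imbalance between arms of about 900 is random error that the confidence interval already covers. Adjustment would reduce it; it would not correct a bias.
- **That the gain is known.** Every hazard ratio and covariate distribution is assumed, and the four effects are mostly raised together. R² on uncensored times stands in for a censored flexible parametric model. At the low end the ITT gain is half a point.

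The objection that a late change has a credibility cost also stands. The SAP is finalised and the trial is open-label, so many of those involved know the allocations.

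**Conclusion.** The point holds as a minor efficiency opportunity for the primary ITT analysis. As described, the model names only factors likely to capture little of the prognostic spread, while better predictors are collected and planned for other uses. Under the assumed hazard ratios, adding them would cut the variance of the RMST difference by about 2–16% and move ITT power from 89% to roughly 89.5–93.5%. No figure is offered for PP. Country was not part of these simulations, so no gain is claimed for it. The conclusion falls away if the SAP already includes these covariates.

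**What to change.** Check the SAP first. If it does not already do so, make a dated amendment before any comparative data are seen. The amendment should specify:

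- a primary model with the stratification factors plus age as a continuous spline, sex, FRAIL score and recruitment source, with country optional;
- the 24-month RMST difference obtained by standardisation over the whole sample, with a delta-method or bootstrap confidence interval;
- a simple rule for imputing missing baseline covariates;
- the strata-only model as a sensitivity analysis.

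No new data are needed and the estimand does not change. The costs are a late amendment to a finalised SAP in an open-label trial, imputation of a few baseline values, and slightly more dependence on model form. To protect credibility, the amendment should record that those who wrote it had seen no outcomes by arm.
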